## Abstract

Although several interventions that target obesity have been examined, the success of these interventions in generating and maintaining positive results has yet to be confirmed. This study protocol therefore presents a trial aimed at analyzing the effectiveness of a well-being-centered acceptance and commitment therapy (ACT)- and mindfulness-based group intervention following the valued-based healthy living (VHL) approach (Mind&Life intervention) for individuals experiencing overweight-related distress. A randomized controlled trial with two parallel groups will be conducted in 110 adults attending primary care units with overweight or obesity. Participants will be randomly allocated to one of the two study conditions. Interventions will either be the treatment as usual (TAU) or the Mind&Life intervention—an ACT- and mindfulness-based intervention—plus the TAU intervention. Quality of life, weight self-stigma, general health status, eating habits, physical activity, eating behavior, anthropometric, body composition, cardiovascular, and physiological variables, as well as process variables, will be examined at baseline, posttreatment, 6-month follow-up, and 1-year follow-up. This trial aims to offer a novel psychological approach for addressing the psychological and physical impairments suffered by people with overweight or obesity in the current environment. ClinicalTrials.gov identifier: NCT03718728.

## 1. Introduction

Obesity is a chronic disease of multifactorial etiology, and due to a progressive increase in prevalence in recent decades, this condition is now regarded as a worldwide public health issue [1]. The excessive accumulation of body fat is clearly harmful to health, as it is linked to numerous noncommunicable diseases including diabetes and cardiovascular complications [2]. Furthermore, the economic costs resulting from obesity are estimated to represent around 0.7–2.8% of a country’s total health care expenditure [3].

This health condition has a considerable impact on psychological well-being, as individuals categorized as obese often experience multiple forms of discrimination, which adversely affects subjective well-being and health-related quality of life [4,5]. Moreover, weight-related stigma and weight self-stigma are linked to psychological distress (i.e., depression and anxiety) [6], while internalized stigma is also associated with a lower quality of life [7].

Primary care units in the Spanish health care system currently use standard weight-related interventions based on diet and physical activity guidelines. Although these interventions appear to be effective for initial weight loss, long-term weight management is a challenge due to weight regain, with multiple factors determining weight maintenance [8,9]. These interventions, however, have proven to be successful in reducing weight regain for up to 12 months when compared with controls [10]. Additionally, the long-term effectiveness of lifestyle interventions for improving emotional aspects and quality of life is questionable [11,12]. One possible explanation for this could be that health-related quality of life is positively associated with the amount of weight lost, and as previously mentioned, these interventions are ineffective for weight loss maintenance [13].

Several studies have shown that psychological factors play a determining role in weight management behaviors [14]. Whereas interventions based on various psychological approaches have been evaluated in terms of effectiveness for weight loss [15], the results have not led to consistent conclusions. For instance, cognitive-behavioral therapy (CBT) has been considered the most preferred intervention for obesity as it has been shown to be effective in improving cognitive and behavioral outcomes, along with weight loss [16,17,18]. In contrast, studies have also shown the ineffectiveness of CBT in targeting emotional aspects [17,19] and weight loss in both the short and long term [19,20]. Motivational interviewing (MI) has also yielded mixed results, with some studies demonstrating a greater efficacy for weight management compared with a control group and others indicating nil to modest efficacy [21,22,23]. Moreover, although the results suggest that MI promotes overall quality of life in people with overweight or obesity, this appears to depend on weight loss [24].

Third-wave cognitive-behavioral therapies in weight management treatments have shown more promise than standard behavioral interventions in the short, medium, and long term [25]. One such therapy is acceptance and commitment therapy (ACT), which is a relatively new psychological approach based on functional contextualism [26]. Within the context of weight management, ACT proposes the alignment of healthy behaviors with deeply held personal values and commitment to them, which function as an anchor when facing challenging situations and promote motivation to persist behaving healthfully [27,28,29]. Likewise, ACT suggests mindfulness to facilitate awareness of unwanted internal or external events that could trigger unhealthy behaviors (e.g., emotional hunger, self-stigmatizing thoughts) and acceptance to address those cues rather than trying to avoid, control, or alter them [27,28,29].

The use of ACT has shown the most consistent evidence of effectiveness for weight management in adults with overweight or obesity after 18 months [25]. One ACT-based study reported that those who received acceptance-based strategies showed an increased probability of maintaining a 10% weight loss and experienced a higher quality of life at 2-year follow-up [30]. Acceptance-based strategies also appear to be particularly beneficial for individuals who show high levels of emotional eating [31,32], a psychological factor that has a direct negative impact on weight management [33]. Furthermore, Sairanen et al. suggested that ACT-based interventions increase weight-related psychological flexibility, intuitive eating, and mindfulness [34]. Interventions based on the latter have also been effective for reducing weight and targeting psychological outcomes such as eating behaviors, problematic eating attitudes, depression, and anxiety [35,36]. In addition, developing mindfulness abilities protects an individual from transforming weight-related stigma into unpleasant emotional symptoms [37].

According to the existing literature, studies evaluating the effect of ACT and/or mindfulness in people with overweight or obesity have shown that these strategies are not only effective for quality of life enhancement [25,38] but are also the most successful for targeting emotional eating [33]. Moreover, weight-related experiential avoidance—a process directly targeted in ACT interventions and mindfulness—mediates changes in emotional eating and weight control [39]. Further, these positive results appear to be independent of weight-related outcomes [30]. Besides, ACT shows promise for reducing weight self-stigma [40,41,42] and psychological distress [43,44], although some inconsistent findings have also been found in the latter variable [45].

Nowadays, two distinct but related ACT approaches focusing weight management issues are distinguished [29]: Acceptance-based behavioral treatment (ABT) and values-based healthy living (VHL). On the one hand, ABT is built upon standard behavioral weight loss interventions, focusing on the usual weight-control goals. However, this approach considers the inclusion of acceptance-based strategies and clarification and commitment to values to sustain weight control efforts. On the other hand, VHL purposes to sweep away the usual weight loss agenda and is centered mainly on clients’ overall quality of life targeting broader values work. That is, this perspective’s aim is to place healthy behaviors firmly into meaningful living context rather than focusing on a concrete weight loss.

In this line, more recently, the well-established weight-normative approach for addressing obesity-related issues has been brought into question. This perspective places weight as the principal determinant of health or disease. Therefore, efforts to enhance physical well-being are focused mainly on weight loss. However, the weight-normative approach involves an increase in perceived and internalized weight stigma, which in turn decreases psychological well-being and physical health while promoting unhealthy eating behaviors [46]. Accordingly, two ACT-based studies in line with the VHL perspective adopting psychological well-being-related variables as primary outcomes found positive results at posttreatment and 3-month follow-up in psychological distress, quality of life, weight-related stigma, self-criticism, eating behaviors, and physical exercise [43,44]. Moreover, a secondary outcome of these therapies was that they were effective in reducing weight, which suggests that these programs could represent another useful strategy for promoting psychological and physical well-being. However, more studies of interventions based on the VHL perspective with longer follow-ups are needed to assess their efficacy in generating and maintaining positive results for obesity-related issues.

The primary aim of this study is to evaluate the effectiveness of a well-being centered ACT- and mindfulness-based group intervention following the VHL perspective in conjunction with the treatment as usual (TAU) (Mind&Life intervention) in comparison with TAU alone. The measured outcomes will be quality of life, weight self-stigma, general health, eating habits, physical activity, and eating behaviors (i.e., emotional eating, restrictive eating, and external eating) of people with overweight or obesity in the short, medium, and long term. It is hypothesized that, in comparison with people receiving TAU (control group), those receiving the Mind&Life intervention (experimental group) will show a greater improvement in these outcomes in the short, medium, and long term.

A secondary goal of this study is to examine the effectiveness of the Mind&Life intervention when considering anthropometric measures (i.e., weight, body mass index (BMI)), body composition measures (i.e., body fat percentage, waist and hip circumference), cardiovascular measures (i.e., blood pressure), and physiological measures (i.e., lipid and glucose profile) at the short, medium, and long term. It is anticipated that the experimental group will show a greater improvement in these variables than the comparison group in the short, medium, and long term. In addition, this trial aims to analyze the mediating and moderating role of various process measures (i.e., psychological flexibility, weight-related psychological flexibility, mindfulness abilities, self-compassion, valued living, and cognitive fusion) in the relationship between the Mind&Life intervention and all outcome measures. We will also examine the mediating and moderating role of weight self-stigma and emotional eating in the relationship between the Mind&Life intervention and all outcome measures.

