### 2.10. Data Analysis

Primary, secondary and process-outcomes will be analyzed using the statistical program SPSS version 26.0 for Windows (IBM Corp., Armonk, NY, USA). Taking into account the aims of the study, the effects of the Mind&Life program will be examined by analysis of variance (ANOVA) and/or covariance analysis (ANCOVA), with group as the independent or fixed variable (experimental or control) and all study outcomes as dependent variables. If any difference in relation to a variable exists at baseline, it will be introduced as a covariate in the analyses. Likewise, when making comparisons at follow-up points (6-month and 1-year follow-up), pretreatment–posttreatment changes will also be introduced in the analyses as covariates. To estimate effect sizes, Cohen’s *d* will be calculated where values between 0.2 and 0.4 will indicate small effects; between 0.5 and 0.7, medium effects; and above 0.8, large effects [70]. Additionally, we will use multiple regression in order to predict the variables that best explain changes in the quality-of-life criterion variable. For mediation and moderation analyses, AMOS software will be used. For each test, values of *p* ≤ 0.05 will be considered significant.

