## 4. Conclusions

Overall, the aim of the current work is to provide data that could indicate the long-term effectiveness of ACT- and mindfulness-based treatments following a VHL approach for individuals with overweight or obesity. This work also aims to identify the specific processes that underpin any long-term behavioral changes observed while allowing us to ascertain whether a shift away from the weight-normative approach could be a viable option for promoting the overall well-being of these individuals.

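### Eight candidate mediators and moderators are tested against all outcomes at 5% per test with no named pair: false moderator findings are likely, false mediation findings less certain

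*Protocol article*

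**What the plan says.** The secondary aims at the end of section 1 state that "this trial aims to analyze the mediating and moderating role of various process measures" and list six of them: "psychological flexibility, weight-related psychological flexibility, mindfulness abilities, self-compassion, valued living, and cognitive fusion". Two more candidates follow: "We will also examine the mediating and moderating role of weight self-stigma and emotional eating". Both sentences set the scope as the role of these variables "in the relationship between the Mind&Life intervention and all outcome measures". That makes eight candidates, each considered as mediator and as moderator, for every outcome.

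Section 2.10 gives this work one sentence of its own, "For mediation and moderation analyses, AMOS software will be used", and closes with a general decision rule: "For each test, values of *p* ≤ 0.05 will be considered significant". Section 1 states directional hypotheses for the primary and secondary outcomes but none for any mediator or moderator.

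The stated use of the results varies. The Discussion uses the verb explore for self-stigma and emotional eating only. For the process measures it expects help in clarifying mechanisms. Section 4 is firmer: "This work also aims to identify the specific processes that underpin any long-term behavioral changes observed".

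**The concern.** The scope and the decision rule together define a large family of tests, each at 5%, with nothing to separate a planned mechanism claim from a screen. Six of the eight candidates carry no exploratory label, and section 4 presents identifying processes as an aim of the work. The sample size in section 2.3.2 rests on one main effect (quality of life, d = 0.68), so nothing shows that the trial can detect real interactions, and chance results may form a large share of any significant moderators.

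At stake is what the trial can conclude about how the intervention works and for whom. The Discussion foresees use by the regional health service if the intervention proves effective, so mistaken statements of this kind could carry weight. This family is distinct from the between-arm comparisons of the primary outcomes: naming or correcting a primary endpoint would leave it untouched.

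**Working it through.** The article states no error rate for these analyses, so there is no figure of its own to reproduce.

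**Inputs**
- Candidates (section 1): 6 + 2 = 8.
- Outcomes, one per heading: 6 in section 2.8.2 (quality of life, weight self-stigma, general health, eating habits, physical exercise, eating behavior) and 7 in section 2.8.3 (BMI, body fat percentage, waist and hip circumference, blood pressure, lipid profile, glucose, insulin sensitivity), total 13. Subscales and separate readings under one heading are not counted.
- Per-test level (section 2.10): 0.05.
- Correlations between tests: not given, so assumed and varied.

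**Number of moderation tests at one time point:** 8 × 13 = 104. Two are self-pairs (self-stigma with itself, emotional eating with its own questionnaire); without them the count is 102.

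**Expected false positives if no moderation exists:** 0.05 × 104 = 5.2 (0.05 × 102 = 5.1 without the self-pairs). This holds at any correlation.

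**Chance of at least one false positive among 104 tests**
- Independent tests: 1 − 0.95^104 = 0.995.
- Correlated tests, by simulation of two-sided 5% z-tests:

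| Assumed correlation r | All tests equally correlated at r | Moderators correlated r and outcomes correlated r |
|---|---|---|
| 0.3 | 0.949 | 0.978 |
| 0.5 | 0.790 | 0.904 |
| 0.8 | 0.363 | 0.483 |

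**Smallest reading, 8 moderators on one outcome at one time point:** independent, 1 − 0.95^8 = 0.337; 0.247 at r = 0.5; 0.157 at r = 0.8. All exceed the nominal 0.05.

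**Participant-level check.** With 110 × (1 − 0.20) = 88 evaluable participants and 1,500 runs per setting, moderation was tested by the group-by-moderator interaction. Mediation was tested by requiring both paths, group to mediator and mediator to outcome, to be significant. Correlations among candidates and among outcomes ran from 0 to 0.7. Outcomes were counted in two other ways: the 6 primary domains only, and a finer count of 20 (8 primary scales and 12 secondary readings). Chance of at least one false finding at one time point:

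| | 6 outcomes | 20 outcomes |
|---|---|---|
| Moderation, r = 0.5 | about 73% | about 96% |
| Moderation, r = 0.7 | 52% | about 75% |
| Mediation, intervention moves no mediator | 4-11% | 7.5-24% |
| Mediation, intervention moves all eight by 0.5 SD, none affects outcome | 39-78% | 58-98% |

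The mediation rows span all correlations tried. The moderation risk is high on either count. The mediation risk depends on whether the intervention shifts the mediators.

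**The case against.** Several points on the other side have force.

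- A reader might infer that the trial is almost sure to report false process effects. The documents do not support that. The large figures are for moderation, whereas the aim in section 4 concerns mechanisms and so rests on mediation. If the intervention moves no mediator, false mediation findings have a chance of only 7.5-24% even with 20 outcomes. An intervention designed to shift these processes makes the higher range plausible, but the article cannot establish it. Even for moderation, the assumed correlations allow values as low as 36%.
- A reader might also multiply by the three post-baseline assessments, to 3 × 104 = 312 tests and 15.6 expected false positives. The mediation and moderation sentences name no time points, and section 2.8 says only when outcomes are measured. That count is an inference, so the figures here stay at one time point. One separate test per pair is likewise a reading, because section 2.10 names software but no model.
- The list is not arbitrary. The Introduction cites earlier evidence that weight-related experiential avoidance mediates change in emotional eating and weight control, and that people with high emotional eating benefit more from acceptance-based strategies. Neither is turned into a hypothesis, however.
- Model form, hierarchy and correction are often left to an analysis plan, which is not shown. That excuses missing detail. It does not excuse the decision rule, which the article fixes for each test; a later correction would have to depart from that text.
- The primary between-arm comparisons are unaffected, which limits the consequence.

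**Conclusion.** The point stands in a bounded form. Followed as written, the plan applies an uncontrolled 5% threshold to a family of at least 104 moderation tests per time point, plus the mediation tests. With no true moderation, about 5 false positives are expected, and the chance of at least one is roughly 80-90% at an assumed correlation of 0.5. False moderator findings are therefore likely. False mediation findings are possible, but their probability turns on the intervention's effect on the mediators.

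The result rests on counting one outcome per heading, one test per candidate-outcome pair, and assumed correlations. None of the scenarios tried brings the moderation error down to 5%. It is worth correcting before analysis because it bears on a stated aim of the trial, though not on its main comparison.

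**What to change.** In section 2.10, limit the p ≤ 0.05 significance rule to the between-arm outcome comparisons. State that all mediation and moderation analyses are exploratory, that they will be reported as estimates with 95% confidence intervals, and that no significance claim will be made from unadjusted p-values. A false-discovery-rate adjustment across the family is an optional addition.

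If one mechanism claim is wanted, name in advance a single mediator, outcome and time point, for example weight-related psychological flexibility for the IWQOL-Lite total at one stated visit, and test only that at 5%. In section 4, replace the verb identify with explore.

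This needs wording changes only, with no new data and no more participants. The downside is that fewer mediator and moderator results can be called significant.

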## 2. Materials and Methods

This protocol was developed basing on the Standard Protocol Items: Recommendations for Interventional Trials (SPIRIT) statement [47] and registered at ClinicalTrials.gov with reference number: NCT03718728.

### 2.1. Trial Design and Setting

The current trial was designed as a randomized, controlled, nonblinded superiority trial with 2 parallel groups. Randomization will be blocked with a 1:1 allocation. The study will be located in the Faculty of Psychology of the University of the Basque Country (UPV/EHU; Donostia-San Sebastián, Spain).

### 2.2. Patient Involvement

This study was designed by the Mind&Life team, a multidisciplinary group based at the University of the Basque Country (UPV/EHU). This group is composed of researchers, psychologists, and nutritionists working in partnership with nurses and doctors from the Basque Health Service, along with physical activity and sport specialists from the Donostia-San Sebastian council representing the various interests of patients and caregivers.

### 2.3. Participants

#### 2.3.1. Recruitment

The research group will contact the doctors and nursing staff from primary care units in Donostia-San Sebastian with the objective of actively involving them in the recruitment process. Information sheets will be provided which will be distributed among possible participants attending primary care units. Those interested in participating in the study will then contact a research team member, who will then confirm the eligibility of the participant.

#### 2.3.2. Sample

##### Eligibility Criteria

Participants will be eligible if they (1) have overweight or obesity (estimated by BMI ≥ 25 kg/m^2^ and classified by the International Obesity Task Force, IOTF); (2) are between 20 and 70 years old; and (3) seek weight management treatment. Participants will be excluded if they (1) have an eating disorder diagnosis such as binge eating disorder, anorexia, or bulimia; (2) have any psychiatric disorder or intellectual disability that prevents them from taking part in the intervention; or (3) have insufficient knowledge of the language in which the intervention will be implemented.

##### Sample Size

Sample size and power estimation were calculated for 5% alpha error, a 2-tailed test, and 80% statistical power (beta error = 20%). The trial uses a comparison group and experimental group design for which pretreatment–posttreatment differences are expected to have an effect size of 0.68 (Cohen’s *d*) for quality-of-life index. The latter has been elected due to the VHL approach of Mind&Life intervention, since among all primary outcomes, quality-of-life index could best reflect values’ work impact. This effect size is based on that of a previous trial studying an acceptance, mindfulness, and compassion-based group intervention program for people struggling with weight-related issues [44]. Since dropout rates of 4–20% have previously been observed, in the present trial, the sample size and statistical power calculations are based on a 20% attrition rate. Hence, it is estimated that 55 participants per group (110 in total) will be needed to evaluate one of the main outcomes of the study, that is, quality of life.

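### The sample size rests on an undefined pre-post effect (d = 0.68) and baseline enters the analysis only conditionally, so the stated 80% power is not shown to apply to the planned test

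*Protocol article*

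**What the plan says.** **Sample Size (2.3.2).** The calculation was "calculated for 5% alpha error, a 2-tailed test, and 80% statistical power", with quality of life as the sizing outcome. For a design with one comparison and one experimental group, "pretreatment–posttreatment differences are expected to have an effect size of 0.68" (Cohen's d). Its source is given as follows: "This effect size is based on that of a previous trial studying an acceptance, mindfulness, and compassion-based group intervention program". With 20% attrition the section arrives at 55 per group, 110 in total. It names no standardiser, and it does not say whether 0.68 is a change within one arm or a difference in change between arms.

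**Introduction.** The hypothesis is that the experimental group "will show a greater improvement in these outcomes in the short, medium, and long term". That is a statement about change.

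**Data Analysis (2.10).** Effects are tested by ANOVA and/or ANCOVA, "with group as the independent or fixed variable (experimental or control) and all study outcomes as dependent variables". A variable that differs between groups at baseline becomes a covariate; otherwise no baseline adjustment is stated. How a difference is to be judged is not said, though p ≤ 0.05 is the significance level for every test. Pre-post change is named only as a covariate at the 6-month and 1-year comparisons. Cohen's d will be reported, again without naming its SD.

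**The concern.** The effect size in the power statement is expressed on pre-post differences. The analysis section does not tie the tested quantity to that scale, and its stated covariate rule would leave baseline out of most analyses. A given treatment effect has a different standardised size on the change score, on the unadjusted posttreatment score and on the baseline-adjusted score. A power figure for one of these cannot simply be read across to another.

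Two things are at stake. A null posttreatment result might be presented as coming from a trial with 80% power when the test actually run had less. And the reported Cohen's d could not be compared with the planned 0.68 if the two rest on different SDs.

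**Working it through.** **Inputs from the protocol:** two-sided alpha 0.05, power 0.80, d = 0.68, 20% attrition, 55 per group, 1:1 allocation.

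**Assumptions, not in the protocol:** pre-post correlation r of the quality-of-life score; equal SD σ at baseline and posttreatment; a baseline difference judged by a two-sided test at p ≤ 0.05.

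**1. The plan's own figure.** A two-sample t-test at d = 0.68 with 80% power needs 34.9, so 35 completers per arm. Allowing for 20% attrition, 35/0.8 = 43.75, so 44 per arm. The protocol states 55, so its figure is not reproduced. It would arise if the allowance were applied twice (44/0.8 = 55), but that is an inference. The discrepancy is on the generous side and is a separate matter. Below I use the completers that 55 per arm implies: 55 × 0.8 = 44.

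**2. Detectable effect and reference power.** With 44 per arm, 80% power is reached at d = 0.604. Power at d = 0.68 is 88%.

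**3. Moving between scales when 0.68 is a between-arm difference in change divided by the SD of change.**
- SD of change = σ√(2(1 − r)), so the raw effect is 0.68 × σ√(2(1 − r)).
- Unadjusted posttreatment score: d = 0.68 × √(2(1 − r)).
- Baseline-adjusted: the residual SD is σ√(1 − r²), so d = 0.68 × √(2/(1 + r)).

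For example, at r = 0.7 the unadjusted d is 0.68 × √0.6 = 0.527 and the adjusted d is 0.68 × √(2/1.7) = 0.738.

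**4. The conditional rule.** Under randomisation a baseline test at p ≤ 0.05 is positive for a given variable in about 5% of trials. The unadjusted test is therefore run about 95% of the time. I simulated the rule: test baseline, adjust only if p ≤ 0.05, otherwise compare posttreatment scores. Repeated runs differ by about one percentage point, and the table gives that spread.

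| Assumed r | Unadjusted post score: d, power | Conditional rule: power | Change score: power | Baseline always included: power |
|---|---|---|---|---|
| 0.6 | 0.608, 81% | 82–83% | 88% | 94% |
| 0.7 | 0.527, 69% | 70–71% | 88% | 93% |
| 0.8 | 0.430, 51% | 53–54% | 88% | 90–91% |

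The unadjusted test falls below 80% once r exceeds 1 − (0.604/0.68)²/2 = 0.605. At lower correlations it does not: its power is 88% at r = 0.5 and 96% at r = 0.3. With baseline always included, calculated power runs from 97.5% at r = 0.3 to 90% at r = 0.9, and is never below the change-score test.

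**5. Other reading of the standardiser.** Under randomisation the expected between-arm difference in change equals the expected between-arm difference in posttreatment score. If 0.68 is that difference divided by the raw-score SD, the posttreatment d is also 0.68, and the unadjusted test has 88% power at any r.

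**The case against.** The strongest reply is that the protocol never says posttreatment scores will be tested. Study outcomes could mean change, which would agree with the hypothesis and the sample-size section. ANCOVA is named. The Sample Size section speaks of a two-group design, so 0.68 may well be a between-arm effect. An article may also leave the exact model to a fuller document.

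Much of this stands. A reader might infer that the 80% power definitely does not carry over. The documents do not support that. Power is 88% if change is the dependent variable, 88% if 0.68 is in raw-score SD units, and at least about 90% with baseline-adjusted ANCOVA. Nor are change and posttreatment score different endpoints in the sense of different treatment effects: under randomisation they estimate the same difference with different precision.

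A reader might also treat 0.68 as a within-arm gain and subtract what usual care achieves. With an assumed gain of 0.1, 0.2 or 0.3 SD under usual care, power would be 77%, 60% or 42%. But the protocol gives no such gain, and the cited trial is not available to show which kind of effect 0.68 was. The Introduction does say that "health-related quality of life is positively associated with the amount of weight lost", and it regards lifestyle care as effective for initial weight loss. It also calls the long-term benefit of such care for quality of life questionable. This reading remains a possibility without a supported size.

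What the reply does not remove is the covariate rule. That rule is stated, not left to another document, and it makes baseline adjustment depend on chance imbalance. Naming ANCOVA therefore does not secure its power.

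**Conclusion.** The point holds in a limited form: the 80% power is not shown to apply to the planned test, which is different from being shown not to apply. Power for the same effect ranges from about 53% to about 94% over assumed correlations of 0.6 to 0.8. Where it falls depends on whether the posttreatment score is tested under the conditional rule or baseline is always in the model. The low end requires three things together: 0.68 in change-score SD units, the posttreatment score as dependent variable, and a pre-post correlation well above 0.6. The protocol states none of them. The conditional-rule figures also assume that imbalance is judged at p ≤ 0.05; a looser criterion would trigger adjustment more often and bring power nearer to the adjusted values.

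The firm part is that the conditional rule can give up power that the already collected baseline score would provide at no cost. Asking what 0.68 measures is a request for clarification.

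**What to change.** **Data Analysis (2.10).** Replace the conditional covariate rule. Analyse posttreatment IWQOL-Lite total by ANCOVA on group, always including the baseline IWQOL-Lite score. Testing the change with baseline in the model gives the identical treatment estimate, so either may be named. Apply the same rule to the other outcomes that have a baseline measure.

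**Sample Size (2.3.2).** State that 0.68 is taken as a between-arm effect and which SD divides it, and use that SD for the reported Cohen's d. If 0.68 is in fact a within-arm effect, restate the claim: 44 evaluable participants per arm give 80% power for a between-arm d of about 0.60 before baseline adjustment.

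**Cost.** Wording in two sections, with no additional participants, visits or data. The only possible downside is a less favourable power statement if 0.68 proves to be a within-arm figure.
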